# Optimising a digitally delivered behavioural weight loss programme: study protocol for a factorial cluster randomised controlled trial

**DOI:** 10.1186/s13063-024-08320-5

**Published:** 2024-07-13

**Keywords:** Optimisation, Weight loss, Obesity, Overweight, Digital health, Mobile health, mHealth, Multicomponent, MOST framework

## Abstract

**Background:**

Digitally delivered weight loss programmes can provide a convenient, potentially cheaper, and scalable treatment option for people who may need to lose weight. However, outcomes are often inferior to in-person interventions in the long-term. This trial will use principles from the Multiphase Optimisation Strategy (MOST) framework to test whether it can enhance the effectiveness of a commercial digital behavioural weight loss programme. This trial aims to identify an optimised combination of four intervention components to enhance weight loss over a 24-week period. We will also explore which components contribute to improvements in participant retention and engagement with the programme.

**Methods:**

Approximately 1400 adults with a BMI > 21 kg/m^2^ will be enrolled and randomised to one of 16 experimental conditions in a 2^4^ factorial cluster design. The trial will test four intervention components: an introductory video call with the health coach, drop-in webchat sessions with the health coach, goal setting statements, and food diary review and feedback. All participants will receive the core digital behavioural weight loss programme and up to four new intervention components. Participation in the trial will last for 24 weeks. The primary outcome will be weight change at 16 weeks. Other outcomes, measured at 4, 16, and 24 weeks, include programme drop-out and engagement (number of interactions with the three main app functions). Fidelity and acceptability will be assessed using data on component adherence and self-report questionnaires. Decision-making for the enhanced programme will be based on components that contribute to at least a minimal improvement in weight loss, defined as ≥ 0.75kg, alone or in combination with other components.

**Discussion:**

The factorial design is an efficient way to test the efficacy of behavioural components alone, or in combination, to improve the effectiveness of digital weight loss programmes. This trial will test the implementation of the MOST framework in an industry setting, using routinely collected data, which may provide a better way to refine and evaluate these types of interventions in a model of continuous service improvement.

**Trial registration:**

Trial registration: ISRCTN, ISRCTN14407868. Registered 5 January 2024, 10.1186/ISRCTN14407868.

**Supplementary Information:**

The online version contains supplementary material available at 10.1186/s13063-024-08320-5.

## Background

Weight loss, to a body mass index (BMI) within the ‘healthy’ range, has been shown to be beneficial for people living with overweight and obesity but also for people with a BMI below the classification of ‘overweight’ by reducing cardiometabolic risk factors [1]. Population-wide efforts to support people to lose weight are important to reduce the burden of avoidable ill health. The most common intervention for weight loss is dietary and physical activity modification through in-person behavioural support programmes [2]. Although effective, the high costs and resource-intensive nature of such programmes can make them unsustainable for implementation at the population level [3]. New options for effective, accessible, and scalable weight loss interventions are needed.

Digitally delivered programmes provide a convenient, potentially cheaper, and scalable treatment option compared to in-person programmes. A meta-analysis found that compared to in-person interventions, digital interventions led to greater weight loss in the short-term but no difference in the long-term, which could in part be due to poor long-term adherence and retention in digital interventions [4, 5]. Designing and optimising interventions to better retain participants and/or increase weight loss is fundamental to realising the potential of digital interventions.

Mobile health apps are generally an aggregation of intervention components, which are packaged together and offered to participants. Although a standard randomised controlled trial can provide evidence about whether this package works better than a comparator intervention, such designs cannot determine the effectiveness of individual components. Using a randomised controlled trial to evaluate new features individually would require conducting numerous individual studies likely over a long period of time, a process that would lag behind the pace of technological advancement.

The Multiphase Optimisation Strategy (MOST) [6] is an engineering-inspired framework which uses highly efficient randomised experimentation to identify an optimised combination of intervention components before testing this intervention package in a standard randomised controlled trial [6, 7]. Factorial trials offer an efficient design well suited to testing components in a technology-supported obesity intervention [8], as it allows simultaneous testing of the effectiveness of multiple intervention components whilst achieving adequate power using a similar sample size to that needed for a single component [9]. Using the MOST framework, it may be possible to develop more effective behavioural interventions faster, and, when paired with the scalability of digital health interventions, this has the potential to provide considerable public health impact. The present study aims to implement the MOST framework to optimise the effectiveness of a commercial digital behavioural weight loss programme.

### Objectives

The primary objective of this study is to determine if one or more of four new components added to a commercial weight loss programme leads to greater weight loss. The four components to be tested are (1) an introductory video call with the health coach (No vs. Yes), (2) drop-in webchat sessions with the health coach (No vs. Yes), (3) goal setting statements (No vs. Yes), and (4) food diary review and feedback (No vs. Yes). Secondary objectives are to (a) identify which intervention components increase retention and (b) assess whether increased engagement with the programme mediates the association between any observed improvements in weight loss and the four components. The study also aims to explore the fidelity and acceptability of each of the intervention components.

## Methods

The Standard Protocol Items: Recommendations for Interventional Trials (SPIRIT) Checklist and figure are provided in Supplementary Material 1 and Fig. 1, respectively

**Fig. 1 Fig1:**
[figure not shown]
Schedule of enrolment, interventions, and assessments

### Intervention component selection

Four intervention components, each with two possible levels, were selected. A list of 93 possible intervention components was generated based on the behaviour change technique taxonomy [10]. This list was condensed to 20 potentially viable components, each supported by empirical literature-based rationale for why it may improve outcomes. This process was informed by expert consultation with academics and healthcare professionals with knowledge of the factors associated with successful outcomes and research into barriers to success as well as consideration of practicality and logistical aspects in collaboration with the commercial partner. The selection of the components was further informed by feedback gained from user interviews with current programme participants to understand key barriers to programme success. Insights from focus groups with the company’s health coaches were used to co-produce the final four intervention components, which helped to translate user feedback into viable components that were practical to introduce in the programme.

The four selected components are hypothesised to work together to enhance outcomes and target supportive accountability [11]. They are hypothesised to improve weight loss beyond the core programme, an effect that could, in part, be mediated through enhanced engagement with the programme (Fig. 2). The intervention theory is based on the supportive accountability model whereby individuals are more likely to adhere to an intervention when they feel accountable to a coach that is trustworthy, benevolent, with relevant expertise and whom sets clear process-focussed expectations, establishes goals, and monitors their progress.

**Fig. 2 Fig2:**
[figure not shown]
Conceptual model for the optimisation of a digital behavioural weight loss programme, incorporating four new intervention components which target supportive accountability

### Study design

The study will use a 2^4^ factorial cluster design that tests all possible combinations of four intervention components. The new components will be tested as adjuncts to a core digital behavioural weight loss programme, Second Nature [12]. Second Nature provides a 12-month digitally delivered behavioural intervention designed to support people to have a healthier diet and increase their physical activity eating habits to thus achieve weight loss. The trial began on 8 January 2024 and is expected to run until February 2025.

Participants will be assigned to groups of 28–32 and will undergo the programme within these groups. Approximately 1400 participants, ranging from 1344 to 1536 depending on group size, will participate in the trial. Follow-up in the trial will last for 24 weeks. Each group will be cluster randomised to one of 16 experimental conditions (Table 1).

**Table 1 Tab1:** Experimental conditions

**Experimental condition**	**Core intervention**	**Health coach introductory video call**	**Coaching drop-in webchat sessions**	**Goal setting statements**	**Food diary review and feedback**
**1**	Y	Y	N	N	N
**2**	Y	Y	N	N	Y
**3**	Y	Y	N	Y	N
**4**	Y	Y	Y	N	N
**5**	Y	Y	N	Y	Y
**6**	Y	Y	Y	N	Y
**7**	Y	Y	Y	Y	N
**8**	Y	Y	Y	Y	Y
**9**	Y	N	N	N	N
**10**	Y	N	N	N	Y
**11**	Y	N	N	Y	N
**12**	Y	N	Y	N	N
**13**	Y	N	N	Y	Y
**14**	Y	N	Y	N	Y
**15**	Y	N	Y	Y	N
**16**	Y	N	Y	Y	Y

### Eligibility

The study aims to enrol adults with a BMI > 21 kg/m^2^, reflecting the usual profile of users of the app. Table 2 presents the key inclusion and exclusion criteria.

**Table 2 Tab2:** Inclusion and exclusion criteria

**Inclusion criteria**	**Exclusion criteria**
• Adults aged ≥ 18 years • Body mass index (BMI) > 21 kg/m^2^ • Registered to privately access the Second Nature programme during the recruitment window • Able to access the internet with a smartphone or laptop and be willing to instal the Second Nature app on their device	• Past or present diagnosis of an eating disorder • Currently pregnant

### Recruitment

Recruitment is planned to run from January 2024 until August 2024. Participants are recruited to the trial through the routine sign-up process on the Second Nature website (https://www.secondnature.io/). The programme is primarily advertised through various online channels and platforms, such as social media, email marketing, search engine marketing, and affiliate partnerships. All advertisements link directly to the Second Nature website. Participants may also find the website through a personal web search.

### Screening, consent, and baseline assessment

Eligibility criteria will be assessed, and baseline data collected, via Second Nature’s bespoke self-reported health questionnaire which will be completed as part of the sign-up process on the Second Nature website prior to commencement of the programme, with no additional instruction. During the questionnaire, participants will be asked to self-report demographic characteristics (date of birth, and sex), anthropometric measures (body weight and height), health-related conditions (diabetes, physical, and mental health conditions), current pregnancy, and their main priorities and goals for the programme. If the participant is ineligible, a pop-up will explain that they do not meet the eligibility criteria for the Second Nature programme, they will not be able to proceed further, and no identifiable information will be collected.

Participants who meet the eligibility criteria will be able to review and accept the Second Nature Terms & Conditions and Privacy Policy, which involves providing consent to be involved in internal and external research and for their data to be used for academic research purposes (Supplementary Material 2). They will then be able to complete the sign-up process, where they can purchase the programme and input their personal contact details (name, email, and home postcode). After sign-up, participants will receive instructions on how to download the Second Nature app. After downloading the app, participants will also be asked to weigh themselves using their weighing scales and record their baseline weight reading in the app.

Participants have the right to withdraw from the programme, and hence also from the trial, and request that all data that has been collected on them is deleted, with no obligation to give a reason.

### Randomisation

Participants will be allocated to closed groups in which they will undergo the programme. Allocation occurs through an algorithm which assigns participants to groups based on age and sex. Groups consist of male only, female only, and mixed sex groups plus mostly older, mostly younger, and mixed age groups. Only groups that have between 28 and 32 participants will be included in the trial, to ensure a similar number of participants will be included in each experimental condition. Groups in which the number of participants falls outside this range will continue to the standard Second Nature programme. Each eligible group will be cluster randomised to one of 16 experimental conditions. The research team will use computerised randomisation software (MinimPy version 2) to randomly allocate the groups with a minimisation algorithm to balance sex and age across the experimental conditions as much as possible. Randomisation will be performed by a researcher who will not be delivering the intervention and who does not have visibility of the screening process or the allocation of groups.

### Blinding

All participants will be blind to treatment allocation. Due to the nature of the interventions, the health coaches who will be delivering the intervention cannot be blinded, but they will not be involved in data analysis.

### Core intervention

The core intervention, delivered to all participants primarily via a smartphone application, is the ‘core’ phase of the Second Nature programme (Fig. 3). The ‘core’ phase consists of a 17-week behavioural change programme aiming to support people to have a healthier diet and increase their physical activity. Participants will be asked to download the app onto their device, or they can also access the app functions on the Second Nature website and use it throughout the intervention period. Participants will have access to the core Second Nature programme for as long as they continue to pay for it within the 24 weeks of the trial. All content within the app can be translated to other languages as required by the user.

**Fig. 3 Fig3:**
[figure not shown]
Example Second Nature core programme content

At the start of the programme, each participant receives a hard-copy instructional handbook and recipe book. Second Nature provides a 12-month programme consisting of three 4-month phases: (1) ‘Core’ (weeks 1–17), where participants receive support from their peers and health coach, and acquire knowledge of nutrition and habit formation; (2) ‘Growth’ (weeks 18–34), where participants gain a deeper understanding of their new behaviours and reinforce their new habits; and (3) ‘Maintain’ (weeks 35–52) where participants practice the skills they have learned to maintain their weight loss and continue to lose weight. The ‘core’ 17-week programme consists of mentoring from a health coach, who is either a registered dietitian or nutritionist, who delivers personalised support via a text-based messaging service within the app. The messaging support will be provided both privately and within a group chat of around 30 other participants. The minimum standard frequency for group messages is as follows: weeks 1–4: four messages per week; weeks 5–8: three messages per week; weeks 9–15: two messages per week; weeks 16–17: three messages per week. The group chat is monitored by the health coach, any comments or questions are answered, and further conversation is facilitated where possible. The private chat is only visible to the health coach and the participant and allows participants to ask specific questions on topics such as health-related issues and personalised dietary requirements. All participants within each experimental condition will be in the same group chat and will be assigned to the same health coach. Educational information, delivered by plain text, audio, and videos can be accessed by participants through the app (Table 3). Participants can record and view their weight and step count within the tracking section of the app, which can also be viewed by the participant’s health coach. Participants who have low engagement (defined as < 10 interactions with the app in the previous week) receive automated messages to encourage participation. Whilst weight monitoring is typically self-directed in the standard Second Nature programme, participants in this trial will be prompted by their health coach to weigh themselves at four specific timepoints within the programme (baseline, week 4, week 16, and week 24) to increase follow-up.

**Table 3 Tab3:** Educational content during each week of the second nature programme

**Week**	**Topic**	**Description**
1	Kickstart week	Introduction to the programme and healthy habits
2	The psychology of eating	The ‘why’ behind certain food choices and overcoming the common obstacles to weight loss
3	Unpacking nutrition	Introduction to nutrition recommendations and common dieting myths
4	The relationship between weight and health	Set point theory, weight loss plateaus, and ways of measuring progress
5	Breaking and making habits	Habit formation, the value of ‘tiny habits’, and stopping unhelpful habits
6	Appetite and cravings	Managing cravings and understanding factors that influence appetite
7	Mindset	Thinking traps, strategies to overcome common thought patterns, and an introduction to body image
8	Stress and emotions	How stress and emotions affect food choices; introduction to mindfulness and emotional eating
9	Exercise	Common barriers to exercise and strategies to incorporate more exercise into daily life
10	Hunger and fullness	The biology and psychology of hunger and fullness and how to be more mindful of fullness cues
11	Nutrition myths	Counting macros, protein intake, alcohol, sweeteners, and reducing risk of heart disease
12	Sleep	The impact of sleep on weight loss and strategies to improve sleep quality
13	Motivation	Types of motivation and how to find and maintain motivation
14	Taking back control	Preparing for challenging situations, social pressure, and impulsive food decisions
15	Reflect and progress	Tools for the next phase of the programme including building self-belief and managing the food environment
16	Accepting thoughts and emotions	Overcoming emotional eating, accepting difficult thoughts, and managing feeling of restriction
17	Moving forwards	Reflecting on the journey so far before moving to the next phase of the programme

During the ‘Growth’ phase, users can still access all features of the app; however, their group will be merged with another group and their health coach may change. The intensity of the programme decreases during ‘Growth’, the message frequency is a minimum of two messages per week, and participation is encouraged less frequently.

The Second Nature programme has been developed based on several behaviour change techniques [10], shown to be effective in diet and physical activity interventions [13], such as self-monitoring, goal setting, feedback, social support, and instruction on how to perform the behaviour. The Second Nature programme has been previously shown to achieve clinically significant weight loss averaging 7.12 kg in those who weighed themselves at 6 months [14, 15] and averaging 6.2 kg after 12 months [16]. Findings also suggest a potential positive association between programme engagement and weight loss [17].

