### Sample size

The available resource allocated to this trial was 48 groups with an average of 30 participants per group. Considering the resource management principle of MOST [7], and given this allocated sample size, we calculated the available power to detect different effect sizes using the R macro %FactorialPowerPlan (Table 5).

**Table 5 Tab5:** Power calculations

**Cohen’s *****d***** effect size**	**Difference in weight**	**Power**
0.25	1 kg	92%
0.22	0.88 kg	85%
0.188	0.75 kg	75%

Power for this study is based on weight change from baseline to 16 weeks. Specifically, the study aims to assess which intervention components contribute to a more than minimal improvement in weight loss to identify components for inclusion in the optimised intervention. Our definition of at least a minimal difference in weight loss is ≥ 0.75 kg—alone or in combination with other components—at 16 weeks. We assumed a standard deviation of 4 kg from previous studies [26], which translates to a component effect size of *d* = 0.188. From a decision-priority perspective, this optimisation trial aims to screen components for an optimised intervention that could be tested in a future definitive evaluation [7, 27]. Therefore, the criteria to consider an effect important will be set liberally at *p*< .10, which is not uncommon for this phase of MOST methodology [8].

Based on previous studies, we assumed a 50% retention rate (an average of 15 participants per group) [26] and a cluster size standard deviation of 5 participants, an intraclass correlation of 0.01 and set alpha to 0.1. This sample size provides 75% power to detect a 0.75 kg difference in weight loss and 92% power to detect any differences of 1 kg or larger. Therefore, this study is powered to detect any main effects or interactions of these sizes or larger.

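### The protocol puts each whole experimental condition in one group chat with one coach, which contradicts its own 48 separate groups of about 30; if followed, it would leave 16 units instead of 48

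*Protocol article*

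**What the plan says.** The Core intervention section, in the text after Fig. 3, fixes delivery at the level of the condition: "All participants within each experimental condition will be in the same group chat and will be assigned to the same health coach". Shortly before that, the same section gives the size of the chat: "The messaging support will be provided both privately and within a group chat of around 30 other participants".

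Elsewhere the unit is the group:

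- Study design: "Participants will be assigned to groups of 28–32 and will undergo the programme within these groups", and "Approximately 1400 participants, ranging from 1344 to 1536 depending on group size, will participate in the trial".
- Randomisation: "Participants will be allocated to closed groups in which they will undergo the programme", and "Each eligible group will be cluster randomised to one of 16 experimental conditions".
- Sample size: "The available resource allocated to this trial was 48 groups with an average of 30 participants per group".
- Core intervention, after Table 3, on the Growth phase (weeks 18–34): "their group will be merged with another group and their health coach may change". This is the only merging of groups described, and it comes after the 16-week primary time point.

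The Statistical Analysis section names participant ID as the random effect in the primary model. It names no group or coach term.

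**The concern.** The sentence is a rule about who delivers the programme and who shares a chat, so it determines how many independent units the trial has. The coach makes the introductory call, runs the webchats, prompts the goal reviews and gives the diary feedback. Participants who share a coach and a chat will therefore tend to have correlated weight outcomes.

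Under the group reading there are 48 such units, as the power calculation assumes. Under the literal reading there are 16, each about three times as large. Standard errors, degrees of freedom and power all depend on which is true, and the choice of components for the optimised programme rests on these estimates. A reader of the article cannot tell which arrangement was meant from this section alone.

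**Working it through.** **1. Group count against the sentence.** 48 groups / 16 conditions = 3 groups per condition on average. At 28 to 32 people per group, that is 3 × 28 = 84 to 3 × 32 = 96 people per condition, against a chat of about 30. The figure of three is derived and not stated, and minimisation on age and sex need not give exactly three everywhere. Still, no split of 48 groups over 16 conditions lets every condition be a single chat of about 30.

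**2. Reproducing the stated figures with 48 groups.** Inputs from the Sample size section: 15 analysed per group, cluster-size SD 5, ICC 0.01, SD 4 kg, alpha 0.10 (taken as two-sided, since the section does not say).

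- Participant range: 48 × 28 = 1344 and 48 × 32 = 1536, exactly as stated.
- Design effect = 1 + ((CV² + 1)m − 1) × ICC, with CV = 5/15 and m = 15: 1 + (1.111 × 15 − 1) × 0.01 = 1.157.
- Each component level has 24 × 15 = 360 analysed. Effective n = 360 / 1.157 = 311.
- SE = 4 × √(2/311) = 0.321 kg. Power for 0.75 kg = Φ(0.75/0.321 − 1.645) = 0.756.
- For 1, 0.88 and 0.75 kg the normal approximation gives 93%, 86% and 76%. A non-central t with 32 to 46 df gives about 92%, 85% and 74–75%. The protocol states 92%, 85% and 75%.

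The sample size therefore rests on 48 separate groups.

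**3. The same calculation if the sentence were followed.** There are 16 units of 3 × 15 = 45 analysed, and the protocol's ICC of 0.01 is applied to the larger unit.

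- Design effect = 1 + 44 × 0.01 = 1.44 with equal sizes, or 1.46 with unit-size SD 5√3.
- Effective n per level = 360 / 1.44 = 250 (247 with unequal sizes).
- SE = 4 × √(2/250) = 0.358 kg. Power for 0.75 kg = Φ(0.75/0.358 − 1.645) = 0.67.
- With t and 16 − 1 − 4 = 11 df (main effects only): 62–63%. With the six two-way interactions as well, 5 df: 56%.
- Power for 1 kg falls from 92% to about 87% (normal), 83% (11 df) or 77% (5 df).

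**4. Error rate of a participant-only model (large-sample approximation for the 16-week contrast).** True error of the nominal 0.10 test = 2 × (1 − Φ(1.645/√design effect)). With 48 groups this is 2 × (1 − Φ(1.645/√1.157)) = 12.6%, which is a separate matter from the chat and coach sentence. With 16 units at ICC 0.01 it is 2 × (1 − Φ(1.645/√1.44)) = 17%.

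**5. Sensitivity to coach differences.** This step assumes 16 different coaches, one per condition, and a coach share c of the variance on top of the group ICC of 0.01. Neither is in the protocol. Design effect = 1.157 + 45.67c, where 45.67 = 45 × (1 + CV²/3) − 1.

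| c | Design effect | Power, 0.75 kg (normal) | True error, group modelled at ICC 0.01, coach omitted | True error, participant-only |
|---|---|---|---|---|
| 0.01 | 1.61 | 63% | 16% | 20% |
| 0.02 | 2.07 | 54% | 22% | 25% |
| 0.05 | 3.44 | 39% | 34% | 38% |

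The fourth column is 2 × (1 − Φ(1.645 × √(1.157/design effect))). The last column uses the formula in step 4, so it includes the 2.6 points that arise with no coach effect at all.

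**The case against.** The best defence is that the operative design is clear everywhere else and the sentence is a drafting slip. Groups are closed, the group is randomised, the chat size matches one group, and merging is described only for the Growth phase. This largely stands, and it is why the point is a contradiction to reconcile and not a demonstrated design failure.

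Three further objections also stand.

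- Only the chat clause conflicts with the group count. One coach can run three groups, so one coach per condition is compatible with three groups per condition.
- A reader might infer that coach is confounded with the components, with 8 coaches against 8 for each main effect. That needs 16 different coaches, each confined to one condition. The article never gives the number of coaches and does not say that a coach serves only one condition. With a single coach throughout, the problem disappears. Even with 16 coaches, each main effect averages 8 conditions against 8, so coach differences enter as extra cluster-level variance and are not aliased with any one component.
- A group random effect would absorb part of any coach variance, and a condensed article may leave the coach term to a fuller document.

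The defence does not remove the need to act. The sentence is written as a rule for conducting the trial, and the article does not say elsewhere how coaches are assigned.

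**Conclusion.** The sentence contradicts the chat size in its own section, the closed randomised groups of 28–32, and 48 groups over 16 conditions. It is probably a slip for group.

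If it were followed, 16 units would replace 48, and power for 0.75 kg would be about 67% (normal) or 62–63% (t, 11 df) against the stated 75%. These figures assume that the protocol's ICC of 0.01 applies unchanged to units three times as large, so they are illustrative.

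A reader might go further and take 39% power or a 38% error rate as the consequence. The documents do not support that. Those values need 16 distinct coaches and a 5% coach share of variance, both assumed, and the 38% also includes the separate effect of omitting a group term. What can be said is directional: if coaches differ between conditions, power falls further and the participant-only model's error rate rises further above 0.10.

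**What to change.** Reconcile the Core intervention sentence with Study design, Randomisation and Sample size by stating that group chat and health coach are assigned per group. Extract coach ID for each group. In the primary model, include group as a random effect and, where coaches serve more than one group, coach as well.

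If one chat or one coach per condition was in fact used, say so, analyse with the condition-level unit (16) as the independent unit, and restate the power on that basis.

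The cost is one corrected sentence, one variable in the data extract and one or two model terms. Rebalancing coaches across component levels is optional and not part of this fix. It is a design trade-off, because coaches are unblinded and could carry practice from one condition to another. It would also come late, since the article appeared in July 2024 and recruitment was expected to end in August 2024.
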